#### 9.8 SENSITIVITY ANALYSIS

## PRED-AID Study Statistical Analysis Plan (SAP)

Every effort will be made to obtain follow up data for participants including those that stop treatment. The primary analysis method outlined above employs maximum likelihood estimation and thus is efficient for handling missing outcome data under a Missing-at-Random (MAR) assumption. That is, it assumes the probability of missing data is not dependent on the values of the unobserved data themselves, conditional on the observed values of the variables included in the analysis model. If >10% individuals are missing the primary outcome at 120 days, Sensitivity analyses will explore the impact of departures from the main MAR assumption on the primary outcome using a pattern-mixture modelling and multiple imputation approach (11). Imputation under MAR will initially be performed separately within each treatment arm using chained equations following the guidance suggested by White et al (12). The variables in the imputation model will be the same as those in the analysis model without including more auxiliary variables after taking into account of the relative small sample size of this study. Imputations will then be modified to reflect departures from the MAR assumption.

We will investigate the impact of a better or poorer response than that predicted by MAR (lower/higher bone turnover) for participants with missing data. To do so we will define  $\delta$  as the postulated mean difference in the change of bone turnover between the observed and unobserved cases. For each participant in each intervention arm we then modify the MAR imputed observations accordingly by  $\delta$ . Imputed data sets will be analysed using the primary analysis model. Results will be combined across imputed data sets using Rubin's rules. We will repeat the analysis for a range of  $\delta$  corresponding to +/- 10, 20, 30, 40 and 50% of the change of bone turn over 120 days in all observed participants.

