### Study visits:

There will be 3 planned study visits, and 4 scheduled telephone consultations during each study period (total of 6 study visits and 8 telephone consults over both periods). The study visits will

be completed on Day 1 and Day 30 in the first month, and the final study visit of each treatment arm on Day 120. Telephone consultations will be on Days 8 and 15 in the first month, followed by further monthly consults on Day 60 and Day 90. Please refer to Appendix 2 for a schematic of the time and events on each study visit. The time window for completing each study visit is  $\pm 3$  days of the target date. Study visits which are completed outside of this window will require a protocol deviation form.

For each study visits, participants will be asked to attend the Clinical Research Facility at the Hammersmith Hospital at 0800h having fasted from 2200h the night before (permitting small sips of water only) and having taken their first steroid tablet of the day at least 2 hours prior. On arrival, observations including heart rate, blood pressure, weight and waist-hip circumferences will be recorded. Urine will be collected for measurement of additional bone markers. The urine will also be subjected to a pregnancy test in participants of child bearing potential. Routine safety blood tests, and immunological blood samples will be collected during each visit. Bone markers and glycaemic markers will also be measured. Participants will be asked to report any symptoms and to complete the SF-36, Addi-QoL and GNCQ questionnaires during each visit.

On the first day of each study period and during visit 1 (visit 4 in the second period), participants will take their usual baseline steroid replacement therapy. Participants will commence the blinded study medication from Day 2 until Day 120 (visit 3).

At the end of each study period, participants will be asked to return their remaining tablets, which will be used to gauge compliance.

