## 6.7 SAMPLE SIZE

The intention is to recruit 55 participants, allowing for a 20% drop-out rate. With 44 completers analysed there is a minimum of 90% power to detect a 1.5 µg/L effect on osteocalcin with a two-sided test at the 5% level of significance, assuming an estimate of the SD at a single timepoint of 3.0 (5). This assumes cautiously that the correlation between the repeated measurements within patients across the two periods is 0.5, whereas a previous crossover trial(6) showed a correlation of 0.8.

Following a pilot study to elucidate a reference range for osteocalcin in healthy volunteers and patients with AI, it has been shown that individuals can demonstrate reductions of up to 2.4 µg/L in the short

PRED-AID Study Statistical Analysis Plan (SAP)

term after changes in their steroid replacement regimen. It is anticipated that that larger changes in osteocalcin will be seen when patients continue on their new regimens for a longer duration.

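### SAP 9.8 shifts imputed values on both drugs by one delta scaled to the pooled change, so it barely tests drop-out that is informative differently by drug

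*Combined protocol and SAP*

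**What the plan says.** SAP 9.8 is triggered when more than 10% of individuals lack the primary outcome at 120 days. It has three steps.

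- Impute: "Imputation under MAR will initially be performed separately within each treatment arm", using chained equations.
- Shift: δ is defined once, as the postulated difference in mean change between observed and unobserved cases. Then "For each participant in each intervention arm we then modify the MAR imputed observations accordingly by" δ.
- Range: δ takes ten values, from ±10% up to ±"50% of the change of bone turn over 120 days in all observed participants".

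No scenario shifts one drug only or uses different values for the two drugs, and no tipping point is sought.

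Two design features determine how large that range can be. On Day 1 of each period "participants will take their usual baseline steroid replacement therapy" (Protocol 8, Study visits), so each period's change is measured from the usual drug. The inclusion criteria (SAP 6.4) admit people established on either hydrocortisone or prednisolone.

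**The concern.** In a two-treatment comparison, the departures from MAR that bias the result are those that differ by drug. One example is participants who leave because they do badly on one drug. A shift common to both drugs mostly subtracts out of the contrast. Tying δ to the pooled observed change also makes the range shrink when the average change is small, whatever the reason.

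This matters because the plan allows for 20% drop-out, twice the 10% trigger. Participants who withdraw are asked for further data only for the current treatment period (Protocol 4.4 and 11.3), so whole second periods may be lost. No other specified analysis tests MAR for the primary outcome. The per-protocol analysis (SAP 7.2 and 9.9.1) is limited to people who completed all visits. Stable results across the ten scenarios could be read as evidence of robustness when much of that stability comes from the construction.

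**Working it through.** **Inputs from SAP 6.7.** The design statement is "With 44 completers analysed there is a minimum of 90% power to detect a 1.5" (units: µg/L). The other inputs are a two-sided 5% test, an SD of 3.0 µg/L for one measurement, and a correlation of 0.5 between a patient's two periods.

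**The plan's own figure.** SD of the within-patient difference = 3.0 × √(2 × (1 − 0.5)) = 3.0. Then n = ((1.960 + 1.282) × 3.0 / 1.5)² ≈ 42.03, so 43. Power at 44 is 91.3% (normal) or 90.0% (noncentral t). Recruitment is 44 / 0.80 = 55. The sample size reproduces.

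**Yardsticks.** SE = 3.0 / √44 = 0.452 µg/L. The critical value on 42 df is 0.913. Holding the SE there, an observed effect of 1.5 loses significance after a shift of 1.5 − 0.913 = 0.587, and an observed effect of 1.0 after 0.087.

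**Effect of a common δ.** Let pP and pH be the fractions missing on prednisolone and hydrocortisone. In a balanced crossover completed by imputation, with treatment and period in a within-participant model:

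shift in contrast = δ × (pP − pH)

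If pP = pH, the shift is 0 for any δ. A numerical check with 28 participants per sequence and δ = 1 agrees. Equal missingness gave 0, and 3/28 against 8/28 missing gave −0.179 = (3 − 8)/28.

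**Size of δ.** The documents give no expected mean change and no user mix, so these are assumptions:

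- θ is the true drug difference.
- h is the share usually on hydrocortisone.
- Osteocalcin does not change while on the usual drug.

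A hydrocortisone user contributes 0 in one period and θ in the other. A prednisolone user contributes 0 and −θ. Hence:

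pooled change = (2h − 1) × θ / 2, and largest δ = half of that

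| θ (µg/L) | h | largest δ | shift, 20% v 10% missing | shift, 30% v 10% missing |
|---|---|---|---|---|
| 1.5 | 1 | 0.375 | 0.04 | 0.075 (0.17 SE) |
| 1.5 | 0.75 | 0.19 | 0.02 | 0.04 |
| 2.4 | 1 | 0.60 | 0.06 | 0.12 (0.27 SE) |
| 4.0 | 1 | 1.00 | 0.10 | 0.20 (0.44 SE) |
| any | 0.5 | 0 | 0 | 0 |
| 0 | any | 0 | 0 | 0 |

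At h = 1 the largest shift is 0.25 × θ × |pP − pH|. A 20-point imbalance therefore moves the estimate by 5% of the effect.

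**Drug-specific δ, for comparison.** Take 20% missing on each drug, where the common δ gives 0.

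- δ = 1.5 on one drug: 0.20 × 1.5 = 0.30 µg/L (0.66 SE).
- δ = 1.5 in opposite directions: 0.40 × 1.5 = 0.60 µg/L (1.33 SE), just past the 0.587 needed.
- Tipping point for an observed 1.5: 0.587 / 0.20 ≈ 2.9 on one drug, or 0.587 / 0.40 ≈ 1.5 in opposite directions.

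**The case against.** A reader might infer that the planned analysis can never move the result and will always look robust. The formula does not support that: the shift is non-zero whenever missingness differs by drug. Such imbalance is plausible, because a period 1 withdrawal caused by one drug removes period 2 values on the other. A borderline result could change. At h = 1 with a 20-point imbalance, observed effects of about 0.87 to 0.96 µg/L could cross the 0.913 threshold (0.913/1.05 to 0.913/0.95).

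A reader might also infer that the mean change is expected to be near zero. The documents do not say so. Protocol 1.2 expects equivalent outcomes, but SAP 6.7 cites individual reductions of up to 2.4 µg/L and anticipates larger changes with longer treatment. A change common to both drugs could also enlarge δ: Protocol 6.3 supplements all participants with vitamin D and says low levels influence osteocalcin. For a pooled change c, the largest shift under a 20-point imbalance is 0.5 × c × 0.20 = 0.10c. An observed effect of 1.0 would need c = 0.87 µg/L to lose significance, and one of 1.5 would need 5.9.

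Three further points are fair. Protocol 8.1 calls the 20% drop-out allowance conservative, and outcomes are sought after treatment stops, so the trigger may not be reached. SAP 9.1 leaves room for other, unspecified sensitivity analyses. The text of 9.8 does not forbid a δ that differs by drug, although a single value is its natural reading.

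Nor can the imputation step be faulted for ignoring sequence. SAP 6.2 defines the arms as the two sequences, so imputation within sequence may already be intended. SAP 9.6.1 uses the same word for the drug.

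These points limit the claim but leave the cancellation under equal missingness intact, and the plan sets out no scenario that avoids it.

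**Conclusion.** The concern holds in a bounded form. As written, the scenarios barely test departures from MAR that differ by drug. The shift is exactly zero under equal missingness. For a drug effect of 1.5 µg/L it is at most 0.04 µg/L with 20% against 10% missing, and 0.075 with 30% against 10%, against an SE of about 0.45.

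The zero rests only on a common δ, balanced sequences and a within-participant treatment estimate. The small non-zero figures also assume no change on the usual drug, and they take h = 1, which gives the largest δ under that assumption. A mixed group of users or similar drugs would make δ smaller; a common time trend could make it larger. The missing fractions by drug and the user mix are not in the documents. The significance thresholds hold the SE at its design value.

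The primary estimate is unaffected. What is weakened is the reassurance that this sensitivity analysis can give.

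**What to change.** Keep the multiple-imputation approach in SAP 9.8 and change how δ is set and applied.

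1. State δ in fixed units of osteocalcin, for example ±0.5, ±1.0 and ±1.5 µg/L, where 1.5 is the powered difference. Extend the grid as far as needed, because one-drug shifts up to 1.5 would not overturn an observed effect of 1.5 at 20% missing.
2. Apply δ to missing prednisolone-period values only, then to missing hydrocortisone-period values only, then to both in opposite directions.
3. Report the δ at which the conclusion changes, together with the fraction missing on each drug.
4. Say whether the arm in the imputation step means sequence (as in SAP 6.2) or drug (as in SAP 9.6.1).

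The cost is a short SAP revision and a few more imputation runs, with no new data and no change to the primary analysis.

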## 9.9 SUPPLEMENTARY ANALYSIS

### 9.9.1 Pre-protocol analysis

The primary analysis will be repeated on the per-protocol sub-group to evaluate the effect of deviations on the primary results.

## 9.10 SUBGROUP ANALYSIS

Three subgroup analyses are planned for the primary endpoint, and markers of cardiovascular disease, to investigate whether the intervention effect differ in patients:

- 1) Taking bone sparing agents
- 2) Taking anti-hypertensives
- 3) Taking lipid-lowering agents

All subgroup analyses will be undertaken using the primary analysis model. For each subgroup factor the model will be updated to include an additional covariate for the subgroup factor (where required) and the subgroup by treatment group interaction term.

## 11.0 APPENDICES

### 11.1 APPENDIX 1

PRED-AID Study Statistical Analysis Plan (SAP)

**Appendix 1: schematic of study periods and visits** Participants will attend visit 1 on their baseline therapy in both periods. They will be issued with steroid/placebo tablets that are identical in appearance. On Day 2, they will be instructed to take the tablets at the stated set times for a period of 4 months in the first period. This is followed by a 2-week minimum washout period on their baseline steroid replacement therapy, before commencing the second period. Patients will be on baseline therapy for Visit 1 of the second period prior to starting the blinded therapy on Day 2 for 4 months. Patients will randomised to undertake either arm (A) or (B). Arm (A) will involve administration of prednisolone in the first period and hydrocortisone in the second. Arm (B) will involve hydrocortisone in the first period and prednisolone in the second period. The example schematic below is for a participant on arm (A).

**Study Period**  
1  
2

**Drug- Arm (A)**  
Prednisolone  
Hydrocortisone

**On Waking**  
2-5mg  
10mg

**Lunchtime (1200h)**  
Placebo  
5mg

**Late afternoon (1700h)**  
Placebo  
5mg

**First Study Period (e.g. Arm (A) - Prednisolone/Placebo)**

| Time  | Study Visit 1
Month 1
Day 1                                          | Month 1
Day 2                          | Telephone Consult 1
Month 1
Day 8 | Telephone Consult 2
Month 1
Day 15 | Study Visit 2
Month 1
Day 30                                          | Telephone Consult 3
Month 2
Day 60 | Telephone Consult 4
Month 3
Day 90 | Study Visit 3
Month 4
Day 120                                         | 2-week washout period on baseline therapy |
|-------|----------------------------------------------------------------------------|-------------------------------------------|-----------------------------------------|------------------------------------------|-----------------------------------------------------------------------------|------------------------------------------|------------------------------------------|-----------------------------------------------------------------------------|-------------------------------------------|
| 06:00 | Patient takes 1 st tablet of the day at home (Baseline therapy) | Patient starts blinded medication at home |                                         |                                          | Patient takes 1 st tablet of the day at home (Blinded treatment) |                                          |                                          | Patient takes 1 st tablet of the day at home (Blinded treatment) |                                           |
| 08:00 | Record weight, BP, heart rate, waist and hip circumference                 |                                           |                                         |                                          | Record weight, BP, heart rate, waist and hip circumference                  |                                          |                                          | Record weight, BP, heart rate, waist and hip circumference                  |                                           |
| 08:20 | Obtain urine sample (NTX & pregnancy test)                                 |                                           |                                         |                                          | Obtain urine sample (NTX & pregnancy test)                                  |                                          |                                          | Obtain urine sample (NTX & pregnancy test)                                  |                                           |
| 08:40 | Blood profile 1                                                            |                                           |                                         |                                          | Blood profile 1                                                             |                                          |                                          | Blood profile 1                                                             |                                           |
| 08:55 | AE reporting                                                               |                                           | AE reporting                            | AE reporting                             | AE reporting                                                                | AE reporting                             | AE reporting                             | AE reporting                                                                |                                           |
| 09:15 | SHS surveys/GNCQ                                                           |                                           |                                         |                                          | SHS surveys/GNCQ                                                            |                                          |                                          | SHS surveys/GNCQ                                                            |                                           |

### PRED-AID Study Statistical Analysis Plan (SAP)

| Second Study Period (e.g. Arm (A)- Hydrocortisone 10mg / 5mg / 5mg) |                                                                            |                                           |                                             |                                              |                                                                             |                                              |                                              |                                                                             | Study complete
(Patient returns to baseline therapy) |
|---------------------------------------------------------------------|----------------------------------------------------------------------------|-------------------------------------------|---------------------------------------------|----------------------------------------------|-----------------------------------------------------------------------------|----------------------------------------------|----------------------------------------------|-----------------------------------------------------------------------------|---------------------------------------------------------|
| Time                                                                | Study Visit 1 (4)
Month 1
Day 1                                      | Month 1
Day 2                          | Telephone Consult 1 (5)
Month 1
Day 8 | Telephone Consult 2 (6)
Month 1
Day 15 | Study Visit 2 (5)
Month 1
Day 30                                      | Telephone Consult 3 (7)
Month 2
Day 60 | Telephone Consult 4 (8)
Month 3
Day 90 | Study Visit 3 (6)
Month 4
Day 120                                     |                                                         |
| 06:00                                                               | Patient takes 1 st tablet of the day at home (Baseline therapy) | Patient starts blinded medication at home |                                             |                                              | Patient takes 1 st tablet of the day at home (Blinded treatment) |                                              |                                              | Patient takes 1 st tablet of the day at home (Blinded treatment) |                                                         |
| 08:00                                                               | Record weight, BP, heart rate, waist and hip circumference                 |                                           |                                             |                                              | Record weight, BP, heart rate, waist and hip circumference                  |                                              |                                              | Record weight, BP, heart rate, waist and hip circumference                  |                                                         |
| 08:20                                                               | Obtain urine sample (NTX & pregnancy test)                                 |                                           |                                             |                                              | Obtain urine sample (NTX & pregnancy test)                                  |                                              |                                              | Obtain urine sample (NTX & pregnancy test)                                  |                                                         |
| 08:40                                                               | Blood profile 1                                                            |                                           |                                             |                                              | Blood profile 1                                                             |                                              |                                              | Blood profile 1                                                             |                                                         |
| 08:55                                                               | AE reporting                                                               |                                           |                                             | AE reporting                                 | AE reporting                                                                | AE reporting                                 | AE reporting                                 | AE reporting                                                                |                                                         |
| 09:15                                                               | SHS surveys/GNCO                                                           |                                           |                                             |                                              | SHS surveys/GNCO                                                            |                                              |                                              | SHS surveys/GNCO                                                            |                                                         |

**AE:** Adverse Event; **SHS:** Subjective Health Status (including the short form health survey (SF-36) and AddiQoL); **GNCQ:** German National Cohort Questionnaire; **Blood profile 1:** fasting renal, bone and lipid profiles, bicarbonate, full blood count (FBC), glucose, insulin, fructosamine, HbA1c, creatine kinase (CK), Adrenocorticotrophic Hormone (ACTH), cortisol binding globulin (CBG), parathyroid hormone (PTH), vitamin D, bone-specific alkaline phosphatase (BALP), osteocalcin (OC), procollagen type 1 N-terminal propeptide (P1NP); **hs-CRP:** hs-CRP; **hs-Troponin I:** BNP assessment of soluble immunological antigens and assessment of white cell populations.
